## Abstract

**Background::**

Polycystic ovary syndrome (PCOS) is one of the most common disorders of reproductive endocrinology affecting women of reproductive age. Our study aims to explore the feasibility of a full-scale trial to evaluate the efficacy and safety of acupuncture for PCOS.

**Methods::**

This study is a two-armed, parallel, multi-country, multi-center, pilot randomized controlled trial (RCT) for PCOS with oligomenorrhea. We will recruit 60 women aged 20 to 40 years with oligomenorrhea due to PCOS. The participants will be randomly assigned to acupuncture and control groups. The acupuncture group will undergo a total of 40 sessions for 16 weeks with usual care. The control group will be managed with usual care (regular meals, sufficient sleep, and appropriate exercise) only. The primary clinical outcome is mean change in menstrual frequency from baseline to 16 weeks and 32 weeks (follow-up) after the start of the trial. The secondary outcomes are menstrual period, levels of estradiol, luteinizing hormone (LH), follicle-stimulating hormone (FSH), and total testosterone, LH/FSH ratio, antral follicle count and ovarian volume, body mass index, waist hip ratio, acne severity, and health-related quality of life questionnaire scores at 16 and 32 weeks after the start of the trial.

**Discussion::**

This is the first protocol for multi-country, multi-center RCTs for PCOS in Korea and China. The control group in this study will be subjected to usual care (regular meals, enough sleep, and appropriate exercise). The results of this study will provide evidence for future clinical decisions and guidelines.

This trial has been registered at ClinicalTrials.gov (Identifier: NCT04509817).

## Introduction

1

Polycystic ovary syndrome (PCOS) is one of the most common disorders of reproductive endocrinology affecting women of reproductive age. PCOS is diagnosed by the presence of any 2 of the following features: oligo- and/or anovulation, clinical and/or biochemical hyperandrogenism, and ultrasonography findings of polycystic ovaries, with the exclusion of other etiologies.^[1]^ Generally, the prevalence of PCOS is considered between 6% and 10%.^[2]^ PCOS is estimated to account for more than 75% of anovulatory infertility cases.^[3]^

The current first-line pharmacological therapy for PCOS patients is the oral administration of selective estrogen receptor modulators such as clomiphene.^[4]^ However, it is ineffective in 40% of the patients diagnosed with PCOS and is associated with significant side-effects like headaches, bloating, mood swings, and breast tenderness.^[5]^ The use of metformin as an insulin-sensitizing agent is also increasing, but the details of the mechanism underlying its efficacy remain elusive.^[6]^ A recently updated review suggested that the efficacy of metformin alone or combined with clomiphene was inconclusive, and the evidence quality was low.^[7]^ Moreover, combined oral contraceptive pills (OCPs) such as Diane-35 (ethinylestradiol and cyproterone acetate) are used by women with PCOS for controlling menstrual abnormalities, hirsutism, and acne.^[8]^ However, the use of OCPs is inappropriate for women who wish to conceive.^[9]^ OCPs may increase the risk of cardiovascular complications or aggravate obesity, thereby exacerbating the associated signs and symptoms of PCOS.^[10]^

Previous studies have found that acupuncture might be effective in improving menstrual (which means increase and regularization of menstrual period) frequency, ovulation rate, and serum hormone levels.^[^11^–^13^]^ A systematic review demonstrated that acupuncture appears to significantly improve the recovery of menstrual cycles and decrease the body mass index (BMI) and luteinizing hormone (LH) levels in women with PCOS.^[14]^ Meanwhile, another systematic review showed significant pooled benefits of acupuncture treatment, used as an adjunct to medication, on LH level, LH/follicular stimulating hormone (FSH) ratio, testosterone level, fasting insulin level, and pregnancy rates, but the level of evidence was low.^[15]^ The objective of this pilot trial is to explore the feasibility of a full-scale trial evaluating the efficacy and safety of acupuncture in improving menstrual frequency and alleviating other symptoms in patients with PCOS. The hypothesis is that acupuncture treatment is more effective than usual care. We will examine this hypothesis through a multi-country, multicenter, pilot randomized controlled trial (RCT).

## Methods

2

### Study design and setting

2.1

This multi-country, multi-center, assessor-blinded RCT will be performed at the following three hospitals: Acupuncture and Moxibustion Hospital of China Academy of Chinese Medical Sciences (CACMS; Beijing, China), Dongzhimen Hospital (Beijing, China), and Kyung Hee University Hospital at Gangdong (Seoul, Republic of Korea). The study period will be 32 weeks, including 16 weeks of intervention and 16 weeks of follow-up. The study plan is summarized in Figure 1. This study protocol followed the Standard Protocol Items: Recommendations for Interventional Trials guidelines (SPIRIT).

**Figure 1 F1:**
[figure not shown]
Flowchart of the trial.

### Recruitment

2.2

Advertisements will be placed in the local newspaper, on the online advertising platforms and on the homepages/social media platforms of the hospitals to recruit participants. Additionally, posters and brochures will be put up in the 3 hospitals.

### Eligibility criteria

2.3

#### Inclusion criteria

2.3.1

The inclusion criteria are as follows:

1.oligomenorrhea (menstrual cycle >35 days or <8 cycles per year) with at least one of the following 2 criteria:A.Hyperandrogenism (clinical, biochemical, or both);B.Polycystic ovarian morphologic features (≥12 antral follicles of 2–9 mm diameter in either ovary; an ovarian volume **≥**10 mL in either ovary; or both);2.Age 20 to 40 years;3.Voluntary agreement to participation in the trial and provide informed consent prior to treatment.

#### Exclusion criteria

2.3.2

We will exclude women who meet any of the following conditions:

1.Pregnancy, labor, or breastfeeding within the past 3 months;2.Intake of oral contraceptives or ovulation-inducing agents within the past 3 months;3.Severe oligomenorrhea with a menstrual cycle lasting >3 months;4.Menstruation lasting >8 days;5.Premature ovarian failure;6.Resistant thyroid disease, Cushing's disease, congenital adrenal hyperplasia, or hyperprolactinemia;7.Ovarian tumors or adrenal tumors that cause hyperandrogenemia;8.Hemorrhagic disease;9.Severe cardiac, pulmonary, hepatic, or renal diseases, central nervous system disorders, or intake of psychoactive drugs;10.Acupuncture treatment within the past 1 month;11.Participation in other clinical trials within the past 3 months;12.Any other conditions considered inappropriate for inclusion in the trial by the investigators.

### Interventions

2.4

This study protocol follows the Standards for Reporting Interventions in Clinical Trials of Acupuncture (STRICTA) recommendations. The participants will be randomly assigned to an acupuncture group or a control (usual care) group in a ratio of 1:1. They will receive interventions and undergo assessments at scheduled visits. Acupuncture will be performed according to a fixed protocol by Korean and Chinese medicine practitioners who have official licenses and at least 2 years of clinical experience. Patients in the acupuncture group will undergo acupuncture therapy 10 times in 4 weeks for 16 weeks, resulting in a total of 40 sessions. Disposable, sterilized, stainless steel single-use needles (0.25 × 40 mm and 0.30 × 50 mm; Dongbang Medical Co. Ltd, Republic of Korea and Qingdao Dongfang Medical Equipment Co., Ltd., China, respectively) will be inserted at a depth of 10 to 50 mm at acupuncture points located in the head, abdomen, lower back, and upper and lower limbs. In total, 18 needles will be used for each participant in a set. The acupoints include GV20 (Baihui), CV4 (Guanyuan), and bilateral BL32 (Ciliao), ST25 (Tianshu), ST29 (Guilai), EX-CA1 (Zigong), LI4 (Hegu), LR3 (Taichong), SP6 (Sanyinjiao), and SP9 (Yinlingquan) and are based on the traditional medicine theory and consensus among experts about acupuncture and PCOS.^[16]^ The location of the acupuncture points is based on the “Nomenclature and location of acupuncture points”^[17]^ and the consensus of experts. All needles will be stimulated manually by rotation until a needle sensation (“de-qi”) is evoked. The patient will be in the prone position first, and the needle will be inserted at the BL32 acupoint at an angle of 30 to 45° in an inferomedial direction and a depth of 30 to 50 mm. Once the patient feels the “de-qi,” the needle will be immediately removed. The patient will then be shifted to the supine position, and GV20, CV4, ST25, ST29, EX-CA1, LI4, LR3, SP6, and SP9 will be needled to a depth of 10 to 40 mm. After the “de-qi” sensation is felt by the patient, the needles will be kept in place for 20 minutes to maintain stimulation. Furthermore, patients will be advised to manage themselves with usual care, similar to that used by the control group.^[18]^

The participants in the control (usual care) group will be managed with the usual care regimen only. They will receive health advice and lifestyle management brochures regarding diet along with regular meals, sufficient sleep, and appropriate exercise once a month for 16 weeks.

The participants are not permitted concomitant medication like OCPs or ovulation induction that may affect menstrual cycles. And, acupuncture, moxibustion, cupping, and other traditional Chinese/Korean medicine treatments are neither allowed if they are judged to affect the outcome measures.

Adherence to acupuncture will be checked every 4 weeks during the treatment period, and participants who have an adherence rate of less than 70% will be dropped out.

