### Sample size

2.8

We calculated the sample size based on a previous study that used the same variables as ours as the primary outcome.^[12]^ For the current study, the mean difference and standard deviation are assumed as 0.14 and 0.17, respectively, between the acupuncture and control groups. In other words, the effect size for menstrual frequency is assumed to be approximately 0.8. In our study, participants will be randomized into 2 groups in a 1:1 ratio after considering 5% of the significance level (α) and 80% of the power (1−β). Therefore, the present study will include 50 participants in total, divided into 2 groups of 25. Considering a dropout rate of 15%, at least 60 participants are required.

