### Statistical methods

2.13

All statistical analyses will be performed using SAS version 9.4 (SAS Institute. Inc., Cary, NC) with a two-tailed test. The level of significance will be set at 5%. Missing data will be substituted using multiple imputations.

The analysis set will consists of a full analysis set (FAS), per-protocol (PP) set, and safety set. The main analyses will be conducted using FAS. A FAS is described as set that is as complete and close as possible to the intention-to-treat. The efficacy test will be assessed by FAS analysis and PP analysis. The safety test will be assessed by intent-to-treat analysis, as well as by PP analysis.

Baseline characteristics of the groups with continuous data will be compared using an independent *t*-test or a Wilcoxon rank-sum test. Baseline characteristics with categorical data will be compared using a Chi-Squared test or Fisher exact test.

The primary outcome measure in this study will be the mean change in menstrual frequency from baseline to 16 and 32 weeks after the start of the trial. To analyze menstrual frequency as the primary outcome, we will perform an analysis of covariance considering the baseline menstrual frequency as the covariate and treatment group as the fixed factor. Additionally, intra-group menstrual frequency changes from baseline to post-treatment will be analyzed using a paired *t*-test or Wilcoxon signed-rank test.

The methods used to analyze the secondary outcome measures will be the same as those used for the primary outcome analyses. If the data type is categorical, it will be analyzed using a Chi-Squared test or Fisher exact test.

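### The 70% adherence rule can act only in the acupuncture arm and, if it ends outcome collection, can bias the near-intention-to-treat main analysis

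*Protocol article*

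**What the plan says.** Section 2.4 (Interventions) of the protocol article prescribes acupuncture "10 times in 4 weeks for 16 weeks, resulting in a total of 40 sessions". Attendance at these sessions is reviewed at 4-weekly intervals while treatment lasts. The stated consequence of falling short is: "participants who have an adherence rate of less than 70% will be dropped out". For the other arm it says: "The participants in the control (usual care) group will be managed with the usual care regimen only". That care consists of monthly advice and brochures, with no adherence measure and no removal rule stated.

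Section 2.13 (Statistical methods) says: "The main analyses will be conducted using FAS". It defines that set as follows: "A FAS is described as set that is as complete and close as possible to the intention-to-treat". It also provides a per-protocol (PP) analysis, and on missing values it says: "Missing data will be substituted using multiple imputations".

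Section 2.5.1 builds the primary outcome from the average menstrual frequency over the 16 treatment weeks and over the 16 follow-up weeks. Section 2.6 places safety laboratory tests at screening and at weeks 16 and 32. Section 2.8 (Sample size) inflates 50 evaluable women to 60: "Considering a dropout rate of 15%, at least 60 participants are required".

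**The concern.** The adherence threshold is applied after randomisation and depends on behaviour that only one arm can show. A 70% cut-off is a usual way to define a PP set. Here it is written as a reason for a woman to leave.

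If leaving ends outcome collection, a woman dropped at a 4-week check has neither a complete 16-week treatment average nor a follow-up average. The missing values then fall in one arm, for reasons that may be linked to prognosis or response. The main analysis keeps the FAS label but moves towards a comparison of adherent acupuncture women with all controls. The later safety laboratory tests of the same women would be lost too.

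The trial is a pilot, but it tests efficacy and is meant to inform a full-scale trial and guidelines. Adherence and retention are among the things such a pilot should measure, and this rule merges the two.

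**Working it through.** **1. The plan's own figure.** Section 2.8 assumes a difference of 0.14 and an SD of 0.17, so the effect size is 0.14/0.17 = 0.82, taken as 0.8. With two-sided α = 0.05 and 80% power, n per arm = 2 × (1.960 + 0.842)² / 0.8² = 24.5, rounded up to 25. Allowing for 15% dropout, 25/0.85 = 29.4, or 30 per arm and 60 in total. The stated sample size reproduces, and this point does not depend on any error in it.

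**2. Does the FAS drop these women?** No. Section 2.13 excludes nobody from the FAS for low adherence. What may be lost is their observed data.

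**3. Does dropping end outcome collection?** Section 2.4 does not say. Section 2.8 uses the same term for women lost from the evaluable 50, which makes loss of outcome data the natural reading. Stopping needling only, or leaving the PP set only, are other readings.

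**4. How many could be affected?** The article gives no attendance rate, so this step is assumption. Ten sessions per 4 weeks means that under 70% is 6 or fewer. Assume each session is attended independently with probability p. If each 4-week block is judged alone, the share dropped is 1 − (1 − P(X ≤ 6))⁴ with X binomial(10, p). If attendance is judged cumulatively at each check, the thresholds are 7/10, 14/20, 21/30 and 28/40.

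| p | P(X ≤ 6) in one block | Dropped, block by block | Dropped, cumulative |
|---|---|---|---|
| 0.80 | 0.121 | 40% | 18% |
| 0.85 | 0.050 | 18.5% | 6% |
| 0.86 | 0.040 | 15% | 5% |
| 0.90 | 0.013 | 5% | 1.4% |

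**5. Size of the bias.** Let q be the share of the acupuncture arm dropped and e the effect in those women. Take 0.14 as the adherers' effect. This is an assumption, since section 2.8 gives 0.14 only as the overall planning difference. If the missing outcomes are imputed as if the women had adhered, the analysis targets 0.14. The effect in all randomised women is (1 − q) × 0.14 + q × e. For q = 15%:

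- e = 0: 0.85 × 0.14 = 0.119; 0.14/0.119 = 1.176, an overstatement of about 18%.
- e = 0.07: 0.119 + 0.0105 = 0.1295; overstatement of about 8%.
- e = 0.14: 0.140; no bias.
- e = 0.21: 0.119 + 0.0315 = 0.1505; understatement of about 7%.

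With e = 0, the overstatement is 5% at q = 5%, 11% at 10%, 25% at 20% and 43% at 30%.

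**6. If acupuncture has no effect.** Suppose low adherers have a prognosis worse by 1 SD (0.17) in both arms, and only those in the acupuncture arm are unobserved. The bias is q × 0.17, which is 0.0255 at q = 15% and 0.051 at q = 30%. In a simulation with 30 per arm, using a t-test of observed adherers against all controls, the type I error was about 7.7% and 15%. With no prognostic difference it stayed near 5%.

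**The case against.** The strongest reply is that nothing in the article says follow-up stops. Section 2.13 keeps the FAS near intention-to-treat and imputes missing values, and section 2.4 may mean only that needling ends. The imputation model, its use of menstrual data recorded before the woman left, and any sensitivity analyses commonly belong to the analysis plan, which is not shown. All of that stands, and it is why the point is conditional.

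Three stronger readings are tempting, and the documents support none of them.

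- **That the FAS loses poor adherers.** Its definition points the other way; they remain in the set.
- **That the effect is certainly overstated.** A reader might infer that the women dropped are those with side effects or no benefit. The article gives no reasons for missed sessions, which could equally reflect work, travel or improvement. Women dropped late could also have had most of their sessions, up to 27 of 40 on the cumulative reading, so zero benefit is an extreme assumption.
- **That the rule alone exhausts the dropout allowance.** The trial allows for 10 losses (60 − 50). Dropping 15% of 30 women is 4 to 5, about half of that allowance, although it is roughly the acupuncture arm's own share of 5.

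What survives is that the rule is explicit, can act in one arm only, and sits badly with the main analysis unless follow-up continues. Multiple imputation under a missing-at-random assumption does not reliably repair this, because most of the information on acupuncture outcomes would come from women who adhered.

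**Conclusion.** The point holds in conditional form. Section 2.4 sets a one-arm, post-randomisation rule, and section 2.13 plans a main analysis close to intention-to-treat. If the rule ends outcome collection, the FAS estimate moves towards a PP estimate and can be biased, probably but not necessarily in favour of acupuncture.

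The size cannot be fixed from the document. With 5% to 30% of the arm dropped, and an effect in those women between none and the same as in adherers, the overstatement runs from 0% to 43%. At 15% dropped it is about 18%, 8% or 0% for no, half or equal benefit, and the sign reverses if those dropped would have done better. These figures assume that 0.14 is the adherers' effect and that imputed values resemble those of adherers. If only needling stops and outcomes are still collected, this bias does not arise and the defect is one of wording. Either way the two sections need reconciling before data are lost that cannot be recovered.

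**What to change.** Reconcile sections 2.4 and 2.13 with a statement along these lines: women below 70% adherence remain in follow-up and are assessed at weeks 16 and 32, including the safety laboratory tests; they are analysed in the FAS with their observed data; the 70% threshold defines PP membership only; and multiple imputation is confined to women who withdraw consent or are lost to follow-up. Whether acupuncture sessions continue below the threshold is left to the investigators; this change concerns follow-up and analysis only.

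The cost is a short amendment and follow-up assessments for a few more women. The FAS effect may come out slightly smaller.

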### Outcomes

2.5

The time points for measuring the outcomes are presented in detail in Table 1. This study is preliminary, but will be allowed for an extensive evaluation of clinical outcome measures as follows:

**Table 1 T1:**
[figure not shown]
Schedule of enrolment, interventions, and assessments.

#### Primary outcome

2.5.1

The primary outcome is the mean change in menstrual frequency (menstrual cycle/month) from baseline to 16 weeks and 32 weeks (follow-up) after the start of the trial. The menstrual frequency will be assessed to evaluate the improvement in ovulatory functions and restoration of menstruation of PCOS patients.^[19]^ The average menstrual frequency for the last year will be recorded as the baseline evaluation. The average menstrual frequency for 16 weeks during the treatment period will be recorded at a close-out evaluation, and that for another 16 weeks during the follow-up period will be recorded at a follow-up evaluation.

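### The primary outcome has two unranked time points at one unadjusted 5% level, but the sample size covers a single comparison

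*Protocol article*

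**What the plan says.** Section 2.5.1 defines the outcome at two times: "The primary outcome is the mean change in menstrual frequency (menstrual cycle/month) from baseline to 16 weeks and 32 weeks (follow-up". It then describes two distinct measurements. One is the average frequency over the 16 treatment weeks. For the other, "that for another 16 weeks during the follow-up period will be recorded at a follow-up evaluation". The abstract names the same two times, and section 2.13 does so again: "The primary outcome measure in this study will be the mean change in menstrual frequency from baseline to 16 and 32 weeks".

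For the analysis, section 2.13 plans "an analysis of covariance considering the baseline menstrual frequency as the covariate and treatment group as the fixed factor". The model has no time factor, so as written it gives one group comparison per window. Testing is to be done "with a two-tailed test", and "The level of significance will be set at 5" per cent.

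Section 2.8 assumes a mean difference of 0.14 and a standard deviation of 0.17, with "5% of the significance level (α) and 80% of the power (1−β"). It arrives at 25 per group, and at 60 in total after 15% dropout. It mentions one comparison and attaches no time point to the 0.14.

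The article gives no primary time point, testing order or division of the 5%, and does not say whether one or both results must be significant.

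**The concern.** The outcome definition produces two primary comparisons, and the sample size calculation was made for one. A 5% error rate and 80% power describe a single test. With two unranked tests, at least one of these figures needs a further rule before it means anything.

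The windows also ask different questions: whether menstrual frequency differs while acupuncture is being given, and whether a difference persists afterwards. If one result is significant and the other is not, the protocol has no planned interpretation. The headline result could then be chosen once the data are known, in a trial where patients and practitioners are not blinded.

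**Working it through.** **Inputs.** From section 2.8: difference 0.14, SD 0.17, so d = 0.14/0.17 = 0.824 (rounded there to about 0.8); two-sided 5%; 80% power; 1:1 allocation; 25 per arm; 15% dropout. The correlation r between the two test statistics is not in the document. It is an assumption, shown as a range.

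**1. The plan's own figure.** Per arm, n = 2(1.960 + 0.842)² / d².
- d = 0.824: 15.70 / 0.678 = 23.1, so 24. The noncentral t calculation gives 25, with power 81.4%.
- d = 0.8: 15.70 / 0.64 = 24.5, so 25. At 25 per arm the noncentral t power is 79.1%.
- Dropout: 25/0.85 = 29.4, so 30 per arm and 60 in total.

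The stated size is reproduced, for one test.

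**2. Rule A: significance at either time point is success.** With no true effect and r = 0, the error is 1 − 0.95² = 0.0975. For r > 0 it is P(|Z1| > 1.96 or |Z2| > 1.96) under a bivariate normal distribution. The chance of at least one significant result assumes 0.14/0.17 at both times, 25 per arm and the normal approximation, under which a single test has 82.9%.

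| r | Family-wise error | At least one significant if the effect is real at both |
|---|---|---|
| 0 | 9.75% | 97.1% |
| 0.5 | 9.1% | 93.1% |
| 0.8 | 7.8% | 89.3% |
| 0.9 | 7.0% | 87.5% |

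Error exceeds 5%, while the chance of a success goes up.

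**3. Rule B: both time points must be significant.** A joint success cannot be more frequent than success at either time alone, so error is at most 5%. For power, the noncentrality is 0.824 × √12.5 = 2.91. At r = 0 the normal approximation gives Φ(2.91 − 1.96)² = 0.829² = 0.688. The table adds a t-test simulation (40,000 trials per row, 25 per arm, the same effect at both times).

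| r | Normal approximation | t-test simulation |
|---|---|---|
| 0 | 68.8% | 66.1% |
| 0.5 | 72.8% | 70.2% |
| 0.8 | 76.5% | 75.0% |

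Error is kept, while power falls below 80%.

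**4. Rule C: one time point is primary.** A single test at 5% with 25 per arm has 81.4% power (noncentral t) if 0.14/0.17 applies to that time point. Both stated properties hold.

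**The case against.** The strongest reply is that the text permits an innocent reading. Section 2.5.1 treats the 16-week assessment as the close-out of treatment and labels the 32-week one as follow-up. If week 16 is the main test and week 32 only shows persistence, 5% and 80% both hold. That is right as a possibility, but the article never states this order: the abstract and sections 2.5.1 and 2.13 all put both times under the primary outcome on equal terms.

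A second reply is that testing order and multiplicity are often left to an analysis plan, and this is a condensed article. That would answer a complaint about missing detail. It does not remove the mismatch between two items that the article does fix: an outcome definition with two times and a sample size for one.

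A third is that the study is a pilot with a feasibility objective and calls itself preliminary. This lowers the weight. It does not remove the point, because the article also states a superiority hypothesis, uses a formal power calculation and expects its results to inform clinical decisions and guidelines.

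Three stronger readings are tempting and not supported:
- *Error control and power both fail.* They fail under different rules, never under the same one.
- *The false positive rate is nearly double.* That holds only at low correlation. The windows are adjacent averages in the same women, so positive correlation is plausible, and at r = 0.9 the rate is 7.0%.
- *The protocol prescribes two tests at 5% each, with either one sufficient.* It gives a single level without adjustment. Separate tests at that level are the natural inference, but the article does not say so, and it names no success rule.

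**Conclusion.** The point holds as a mismatch inside the protocol: two unranked primary time points, one unadjusted two-sided 5% level, and a sample size for one comparison. The size of the problem depends on the unstated success rule:
- Either suffices: error of about 7% to 9.75%, for assumed r from 0.9 to 0.
- Both required: power of about 66% to 75%, for assumed r from 0 to 0.8.
- One ranked first: no loss.

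The power range is illustrative. It assumes 0.14/0.17 in both windows, and nothing in the article supports an equal effect in the 16 weeks after treatment ends. It also uses an unadjusted t-test; the planned baseline-adjusted analysis could add power, but no baseline correlation is given to quantify this.

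A reader might infer that the 80% power belongs to week 16. Section 2.8 does not say so, and the cited study behind the 0.14 was not available for this check. Given the feasibility objective, and because neither conduct nor sample size has to change, this should be fixed but does not by itself undermine the trial.

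**What to change.** 1. In section 2.5.1, the abstract and section 2.13, name one time point as primary, for example the 16-week treatment period, tested at two-sided 5%. The choice is the sponsor's.
2. Make the other time point a key secondary outcome, tested at 5% only if the primary test is significant.
3. In section 2.8, state which time point the 0.14/0.17 refers to, after confirming from the cited study that it matches the chosen primary time point. If it does not match, the assumption has to be justified again.

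The change is one of wording, and the registered outcome should be brought into line if it reads the same way (the record was not seen). The 60 participants stand, and the primary test loses no power. The price is that the secondary time point can no longer carry the trial's claim alone.

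Keeping both as primary costs more. For 0.14/0.17, testing each at 2.5% gives about 72% power per time point with 25 per arm (noncentral t). Restoring 80% per time point takes 29 (normal) to 30 (t) per arm, so 58/0.85 to 60/0.85, or 69 to 71 randomized. Requiring both at 5% with 80% joint power takes 28 to 31 per arm (normal approximation, r = 0.8 to 0), so 56/0.85 to 62/0.85, or 66 to 73 randomized.

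### The baseline averages menstrual frequency over a full year, but eligibility rules out pill use, ovulation induction, pregnancy and breastfeeding for only 3 months, so an affected woman's baseline need not reflect her natural cycle

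*Protocol article*

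**What the plan says.** All references are to the protocol article.

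- **Baseline (2.5.1):** "The average menstrual frequency for the last year will be recorded as the baseline evaluation".
- **Treatment period (2.5.1):** "The average menstrual frequency for 16 weeks during the treatment period will be recorded at a close-out evaluation". A second 16-week average covers follow-up.
- **Exclusions (2.3.2):** "Intake of oral contraceptives or ovulation-inducing agents within the past 3 months" and "Pregnancy, labor, or breastfeeding within the past 3 months". Also "Severe oligomenorrhea with a menstrual cycle lasting >3 months".
- **Entry (2.3.1):** "oligomenorrhea (menstrual cycle >35 days or <8 cycles per year", so either route is enough.
- **During the trial (2.4):** "The participants are not permitted concomitant medication like OCPs or ovulation induction that may affect menstrual cycles".
- **Use of the baseline (2.13):** it is the reference for the primary change and the covariate in the ANCOVA, with treatment group as the fixed factor. In addition, "intra-group menstrual frequency changes from baseline to post-treatment will be analyzed using a paired" t-test or a Wilcoxon signed-rank test.

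No stated rule removes or adjusts for baseline months spent under one of the listed exposures.

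**The concern.** The plan bars the pill and ovulation induction during the trial because they can alter the cycle. The same reasoning applies to the period that supplies the baseline, yet the look-back for these exposures is a quarter as long as the baseline window. Earlier exposure is foreseeable: the Introduction calls clomiphene-type drugs the first-line drug therapy and says women with PCOS use oral contraceptives to control menstrual abnormalities.

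Section 2.5.1 uses menstrual frequency to judge ovulatory function and the return of menstruation. Pill bleeds, induced cycles and pregnancy or lactation amenorrhoea do not show a woman's untreated state. If they are averaged into the baseline, her change score measures partly the end of the exposure and only partly what happened in the trial. Since the pilot is meant to inform a full-scale trial, a distorted mean change and its spread could carry over into that planning.

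**Working it through.** **The plan's own figure.** From 2.8: difference 0.14, SD 0.17, 5% significance level, 80% power; 2.13 makes tests two-tailed.

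- n per arm = 2 × (1.960 + 0.842)² × (0.17/0.14)² = 23.1, so 24. With the rounded effect size 0.8: 2 × 7.849/0.64 = 24.5, so 25.
- With 15% dropout: 25/0.85 = 29.4, so 30 per arm and 60 in total.

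The sample size reproduces and is not in dispute. The 0.14 serves below as a yardstick.

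**Uncleared window.** 12 - 3 = 9 months, or 75% of the baseline year. This is a maximum.

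**Shift for one affected woman.** Assumptions not in the document: natural rate 0.50/month (a cycle of about 61 days), and 28-day bleeds on the pill, so 365.25/28/12 = 1.087/month. With m exposed months at rate g:

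recorded baseline = [(12 - m) × 0.50 + m × g]/12

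| Exposure | Recorded baseline | Shift | Shift/0.14 | Bleeds in the year |
|---|---|---|---|---|
| 3 pill months | 0.647 | +0.147 | 1.0 | 7.8 |
| 6 pill months | 0.794 | +0.294 | 2.1 | 9.5 |
| 9 pill months | 0.940 | +0.440 | 3.1 | 11.3 |
| 6 months amenorrhoea (g = 0) | 0.250 | -0.250 | -1.8 | 3.0 |

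The pill shift is smaller with a shorter natural cycle. At 45 days (0.676/month) it is +0.103, +0.205 and +0.308 for 3, 6 and 9 pill months.

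**Can such a woman enter?** After 3 pill months she has fewer than 8 bleeds in the year and meets either route. After 6 or 9 she has more than 8, but she can still enter on a cycle longer than 35 days since stopping.

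**Effect on the change score.** A woman who truly gains 0.14, from 0.50 to 0.64, after 6 pill months is recorded as 0.64 - 0.794 = -0.154, an apparent worsening. A woman with no change at all and 6 months of amenorrhoea in the baseline year is recorded as 0.50 - 0.25 = +0.25. Pill bleeds understate improvement; amenorrhoea overstates it.

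**Effect on an arm's mean change.** It equals the share affected times the shift. The share is not in the document, so only a range can be shown: 5% with 3 pill months gives 0.05 × 0.147 = 0.007; 10% with 6 gives 0.029; 10% with 9 gives 0.044; 20% with 9 gives 0.088. The sign reverses for amenorrhoea.

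**Effect on the primary contrast.** When baseline is a covariate, analysing change or the post-baseline value gives the same group coefficient; only the coefficient of baseline differs, by 1. Exposure before randomisation is balanced between arms in expectation. Error in the baseline therefore does not create a group effect. It only lowers the correlation between baseline and outcome, and so the precision that the covariate gains.

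**The case against.** The strongest defence is that the primary comparison is a randomised ANCOVA, so it stays unbiased, and that the sample size claims no gain from the covariate. That stands, and it limits the point. A reader might infer that the estimated treatment effect is biased; the document does not support this.

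A reader might also infer a large loss of power. In an unadjusted comparison of change scores (25 per arm, 60-day natural cycle, SD 0.17 without contamination), power falls from 81% to 79% if 10% of women had 3 pill months, to 62% if 10% had 9, and to 51% if 20% had 9. That is not the planned analysis, ANCOVA limits the loss, and the shares are assumed. No figure for lost precision can be drawn from the document.

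Eligibility narrows the problem. Many long-term pill users would fail the count of cycles per year, and the exclusion of cycles over 3 months may remove some women with long amenorrhoea, although it is not worded for pregnancy or lactation. Neither closes the gap, because the entry criterion is an either/or.

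A one-year baseline also has merit: it averages more cycles. For that reason regression to the mean is no argument against it, since a longer window reduces it. A short clean window has its own error. At 0.50/month, 3 months hold 1 or 2 onsets, giving 0.33 or 0.67, an error of about 0.17. This stands as a cost. But that error has no fixed direction, and it is smaller than the 0.44 shift it replaces in a woman with 9 pill months.

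Finally, a journal article may leave derivation details to the full protocol. Here, however, the article states the rule, and following it as written gives the wrong baseline for affected women.

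**Conclusion.** The point holds in a limited form. As stated, the baseline window and the exclusion look-back let up to 9 of 12 baseline months reflect something other than the natural cycle. For an affected woman the error, in the illustration, is about one to three times the design difference after pill use and nearly twice it, in the other direction, after 6 months of amenorrhoea. These sizes rest on the assumed 0.50/month natural rate and 28-day pill bleeds; 9 months is a worst case.

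Three things are affected: the reported mean change, which is the named primary measure; the value of the only stated covariate; and the within-group paired tests, which have no randomised comparison to protect them. The between-group ANCOVA estimate is not biased. The total effect depends on how many women had such exposures, which the document does not give. This should be corrected, but it does not undermine the primary comparison.

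**What to change.** Define baseline menstrual frequency as the number of menstrual onsets divided by the number of months, counting only those of the last 12 months free of oral contraceptives, ovulation induction, pregnancy and breastfeeding. The present exclusion criteria already ensure at least 3 such months, so eligibility need not change. Use this baseline for the change score and as the ANCOVA covariate.

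Replace the within-group paired tests by within-group mean change with a confidence interval, labelled as descriptive.

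The cost is two history questions on the past year (which exposures, and in which months) and one derivation rule. The baseline becomes noisier in women with few clean months, with a counting error of about 0.17/month when only 3 remain. Women with no exposure keep their full 12-month baseline unchanged.
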